In detail: four Styrian communities were selected according to the postal code as intervention regions because they have well-developed sports club networks. In these urban and rural communities, regional, standardised, sports club based exercise programmes will be provided twice a week. Because the number of inhabitants of three of the communities is relatively small, we decided to selected similar communities as controls and not to randomly select people of the same area for the intervention and control groups. The controls live in four different regions that are similar with regard to size, urban or rural alignment and sports club networks. As soon as the inhabitants of the eight communities have received approval from their health insurance companies for the residential stay in a health resort, they will be contacted and asked whether they agree to the measurement of their physical activity behaviour before the residential stay, and they will also be asked to fill in a questionnaire. If they are willing to take part in the activity analysis, they will have to return a form giving consent to the procedure and providing the assumed start day of the residential stay. Those who do not meet the WHO physical activity guidelines will be eligible for the study and will be asked during their residential stay whether they agree to participate in the study.

### Intervention

During the residential stay in the health resort, members of the intervention group who do not meet the physical activity guidelines based on the accelerometer data will receive a so-called “starter package”. During the stay at the health resort, people who took part in the prior physical activity measurement programme will be informed about the regional programmes if they do not meet the physical activity guidelines.

This starter package will include information about the project, an informed consent form, as well as a voucher for 12 regional, standardised, sports club based exercise sessions which can be attended immediately after the stay. The costs for these 12 sessions will be covered by the project funds so that participants need not pay any fee. Ideally, the beginning of the regional, standardised, exercise programme should be scheduled during the residential stay. “Standardised” means that the instructors will receive an obligatory 18-h training programme, and the sessions will have a defined structure with the following quality criteria [14]:Number of exercise sessions per week: two sessions.Duration of each single session: 90 min.Maximum number of people in a training group: 12 people.Cardiovascular exercise during a single session: ≥40 min of moderate- to vigorous-intensity aerobic activities.Muscle-strengthening activities during one session: ≥30 min; ≥2 sets of ≥6 different muscle-strengthening activities.Coordination and flexibility: will not be performed as a distinct part but it will be integrated in the cardiovascular and muscle-strengthening sections of the programme.Feedback on individual physical activity goals: as a supplement to the standardised exercise programme, individual “physical activity homework” will be prescribed to ensure that the physical activity recommendations can be realised. Furthermore, participants will be encouraged to support each other by identifying helpful behaviour change strategies and applying social support. Ten minutes will be reserved for this at the beginning and end of each session.

The advanced job training will include lectures and a manual with 12 different predefined sessions. Furthermore, health aspects of physical activity will be introduced, as well as extended communications training.

### Control group

During the stay in the health resort, members of the control group will be encouraged to be active in the future. They will receive the brochure entitled “Physical Activity: Health for all” (Bewegung: Gesundheit für alle http://www.fgoe.org/presse-publikationen/downloads/broschueren-folder/bewegungsbroschure-pdf-475-kb/2013-12-06.3369959292) [15]. The brochure covers the following topics:Effects of physical activity.How to become active and how to stay active.Fitness checks.Components of health-enhancing physical activity.Body weight.Planning your activities.

### Analysis of sub-groups

At the 12-months follow-up, the intervention group will be divided into sub-groups for further analysis:Sub-group I: participants who attended ≥75 % of the 12 exercise sessions of the standardised programme during the last 12 months.Sub-group II: participants who attended ≥25 % and <75 % of the 12 exercise sessions of the standardised programme during the last 12 months.Participants who did not attend 25 % of the 12 exercise sessions of the standardised programme.

The sub-group analysis is necessary because we aim to determine if regular long-term participation leads to different levels of physical activity compared to non-regular participation. Another hypothesis is that finishing the initial 12-session programme is the most powerful predictor for a high level of MVPA. Thus, the sample size calculation is based on between-group differences in MVPA.

### Sample size calculation

For the sample size calculation, the difference in minutes of MVPA measured in bouts ≥10 min is considered as a suitable parameter for health-enhancing physical activity [16]. According to several studies, MVPA is an appropriate parameter for that purpose [17, 18]. Jung et al. [16] evaluated the changes in MVPA after a supervised exercise intervention in a similar cohort (male and females, aged 51(10)) years suffering from prediabetes). After the intervention, MVPA was changed by 44.5 (72.2) minutes. Due to the fact that the intervention-induced changes in our study are supposed to be similar, we considered the changes in MVPA of the above-mentioned study to calculate the sample size in our study.

Given a clinically relevant difference of 44.5 min of MVPA between the intervention and control groups, a standard deviation of 72.2 MVPA of the differences and a two-sided significance level of 0.05, a sample size of *n* = 42 per group is needed to reach a statistical power of 80 %. Since drop-outs and those lost to follow-up may have an inestimable effect on the assumed standard deviation of the differences, the sample size will be increased to *n* = 48 persons per group. Expected value μ1 (intervention) = 84.1 MVPA, μ2 (control) = 39.6 MVPA. Calculations were undertaken via: http://www.clinical-trials.de/de/Werkzeuge/werkzeuge.html

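### The 44.5 min planned between groups is the change reported after a supervised programme, used undiluted although the protocol expects incomplete uptake, so the stated 80 % power holds only if the whole intervention group achieves that effect

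*Protocol article*

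**What the plan says.** All of the following is from the protocol article.

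- **Source of the effect.** The Sample size calculation section relies on a cited study that "evaluated the changes in MVPA after a supervised exercise intervention in a similar cohort", and reports: "After the intervention, MVPA was changed by 44.5 (72.2) minutes". The transfer is justified in one clause: "Due to the fact that the intervention-induced changes in our study are supposed to be similar".
- **Use of the effect.** The next paragraph begins "Given a clinically relevant difference of 44.5 min of MVPA between the intervention and control groups". It takes 72.2 as the SD and "a two-sided significance level of 0.05", and concludes that 42 per group "is needed to reach a statistical power of 80" %. The planned means are 84.1 (intervention) and 39.6 (control), which differ by exactly 44.5.
- **Increase.** The 42 becomes 48 per group on account of drop-out and loss to follow-up. Non-uptake is not mentioned.
- **Uptake elsewhere.** Study objectives makes the number who take part in the programmes the first research question. Analysis of sub-groups splits the intervention group by attendance, the lowest band being "Participants who did not attend 25 % of the 12 exercise sessions of the standardised programme". The Discussion foresees people who leave the programme or never begin it.
- **Controls.** Under Control group, "members of the control group will be encouraged to be active in the future", and they receive a brochure. The Background says that resort stays include lifestyle intervention. It also says that most such residential interventions lack lasting effect, and the Abstract's discussion says the same of these stays. No expected control change is stated.
- **Total.** Eligibility and recruitment gives 194 participants; 48 per group gives 96.

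**The concern.** A change after a supervised programme estimates what happens to people who are in that programme. The contrast planned here compares everyone in the intervention regions with everyone in the control regions, and what the intervention group is given is information and a voucher. The mean difference between these groups carries the programme effect only in proportion to uptake. It also carries only the part of the effect that exceeds what controls achieve. The section makes no allowance for either and states no assumption about either.

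At stake is the stated power, the only justification given for the trial's size. If it is too favourable, a non-significant comparison would say less about linking resorts with sports clubs than the plan implies.

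**Working it through.** **Inputs.** From the Sample size calculation section: difference Δ = 44.5 min, SD = 72.2 min, two-sided α = 0.05, power 80 %, equal groups, n = 42 raised to 48. From Eligibility and recruitment: 194 in total, or 97 per group if split evenly (an assumption). Uptake u and control change c are not given, so both are shown as ranges.

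**Step 1: reproduce the plan's figure.** Normal approximation for two independent means:

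n = 2 (1.960 + 0.842)² (72.2 / 44.5)² = 41.3, so 42 per group.

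The two-sample t calculation gives 42.3, so 43. One-sided (33) and paired (23) calculations do not match. The plan therefore used a two-sided, two-group formula with 44.5 as the between-group difference. By the t calculation, power at Δ = 44.5 is 80 % at 42 per group, 85 % at 48 and 99 % at 97. The step from 42 to 48 corresponds to a loss of 1 − 42/48 = 12.5 %.

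**Step 2: the difference with incomplete uptake.** Let attenders change by 44.5, and let controls and non-attenders both change by c. Then:

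- intervention mean change = u × 44.5 + (1 − u) × c
- control mean change = c
- difference = u × 44.5 + (1 − u) × c − c = u × (44.5 − c)

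The plan's 44.5 is the case u = 1, c = 0.

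**Step 3: power with c = 0** (two-sample t, SD held at 72.2):

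| Uptake | Difference (min) | 42 per group | 48 per group | 97 per group |
|---|---|---|---|---|
| 100 % | 44.5 | 80 % | 85 % | 99 % |
| 80 % | 35.6 | 61 % | 67 % | 93 % |
| 60 % | 26.7 | 39 % | 43 % | 73 % |
| 50 % | 22.25 | 29 % | 32 % | 57 % |

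**Step 4: sensitivity to a control gain.** The value c = 10 min is chosen for illustration and is not in the documents:

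| Uptake | Difference (min) | 42 per group | 48 per group | 97 per group |
|---|---|---|---|---|
| 100 % | 34.5 | 58 % | 64 % | 91 % |
| 75 % | 25.9 | 37 % | 41 % | 70 % |
| 50 % | 17.25 | 19 % | 21 % | 38 % |

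**Step 5: difference detectable with 80 % power, and the uptake it implies when c = 0** (detectable difference / 44.5):

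| n per group | Detectable difference (min) | Uptake needed |
|---|---|---|
| 42 | 44.7 | 100 % |
| 48 | 41.7 | 94 % |
| 97 | 29.2 | 66 % |

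**The case against.** **The formula is correct.** A reader might infer a calculation error. There is none: 42 per group follows from the stated inputs. This is a matter of the planning assumption and the power claimed from it.

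**An unchanged control group fits the protocol's premise.** A reader might infer that the protocol contradicts zero control change, because controls have the same kind of stay, encouragement and a brochure. The documents do not go that far. They state no control change, and the Abstract and Background say that effects of such stays fade. A control gain is possible but belongs in a sensitivity analysis. Nor does choosing everyone for low baseline activity settle it: regression to the mean that is equal in both groups cancels. It would matter only if the borrowed 44.5 itself contained some, and that cannot be checked here.

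**Subtracting a control gain from u × 44.5 would overcorrect.** That gives non-attenders no gain while controls gain c. Non-attenders have had the same kind of stay and the same selection, and the Discussion says that people outside the programme may become active. At 50 % uptake and c = 10 that version gives 12.25 min instead of 17.25.

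**The before-after reading is an inference.** The article says only that MVPA changed after the intervention. This is the natural reading, but even if 44.5 were a controlled contrast, dilution by non-uptake would remain.

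**The evidence on uptake gives no rate.** The first research question concerns eligible people, and those who consent may attend more often. The attendance bands show that low attendance was foreseen, not how common it will be. This stands, and is why a range is shown.

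**The target might be attenders.** The second research question compares participants with non-participants, and the sub-group section links the sample size to its attendance hypotheses. But the Sample size calculation section names intervention versus control explicitly.

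**Power may be better than shown.** With 97 per group, 80 % is kept down to about 66 % uptake when c = 0. The planned baseline-adjusted ANCOVA may also be more efficient than the calculation assumes, so 80 % is not strictly an upper limit. Both points stand. However, the section claims its 80 % at 42 per group, and the article does not explain the 194.

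**Conclusion.** The concern holds as a fault in the planning input. The protocol uses a change seen after a supervised programme as the full intervention-versus-control difference, while its own objectives, attendance bands and Discussion expect part of that group not to take the programme up. The stated 80 % applies only if the whole group achieves the supervised-programme effect over controls.

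Over the illustrative range of 80 to 50 % uptake, power is 61 to 29 % at 42 per group, 67 to 32 % at 48, and 93 to 57 % at 97. These figures rest on an SD of 72.2 at every level of uptake, on uptake meaning an effect equal to that of the cited programme, on non-attenders changing as controls do, and on no control change. How serious the loss is depends on the true uptake and on whether 96 or 194 is the intended total. That a null result would in fact be misread is a risk, not something the documents show.

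**What to change.** In the Sample size calculation section:

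1. Stop presenting 44.5 min as the expected difference between the groups. Describe it as the change reported after the cited supervised programme.
2. State the planned difference as u × (44.5 − c), with u the expected uptake and c the change assumed for controls and for non-attenders alike. Give the reasons for the values chosen.
3. Show power over a range of u and c, for example uptake 50 to 100 % and c from 0 to 10 min, at the final total.
4. Reconcile 48 per group with the 194 participants in Eligibility and recruitment before doing so.
5. If feasibility fixes the size, replace the 80 % claim with the difference detectable at 80 % power: 44.7 min at 42 analysed per group, 41.7 at 48, or 29.2 at 97.

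The cost is one rewritten paragraph and a less favourable stated power. No extra participants are required.

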### Statistical analyses

All the statistical analyses will be performed with IBM® SPSS® Statistics for Windows, Version 20 (IBM Corp., Armonk, NY, U.S.). P-values <0.05 will be considered to be statistically significant, and all tests will be two-sided. Data exploration using descriptive statistical analysis and inferential statistics will be performed. The sample data will be carried out by frequencies or percentages (categorical variables), means and standard deviations (continuous variables) and graphics. T-tests and chi-square tests will be used to compare the groups. If a normal distribution is not met, non-parametric tests will be applied. Analysis of covariance (ANCOVA) (comparing parameters after the intervention and after the follow-ups) between the intervention and control groups will be adjusted for the baseline values as the covariate analysis is performed.

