A major strength of the study will be the fact that different sectors will be cooperating and that physical activity will be measured objectively. Another strength will the process evaluation with the objective to learn about the implementation of exercise referral in medical settings. The study intervention itself will be another strength: the regional, standardised, exercise programmes have been developed by scientists, together with representatives of sports clubs. If the study participants attend the exercise programmes twice a week, they will almost meet the WHO physical activity recommendations.

A limitation of the study might be the recruitment that will be undertaken during the stay at the health resorts. Although the procedure is described in detail, it will be undertaken by employees of the resorts, and not by the study stuff. This is an important issue, because taking sustainability into account, it is the staff in the health resorts who should encourage people to attend regional, standardised, exercise programmes after their stay at health resorts in the future. Therefore, one of the most important questions in the process evaluation is how the staff in the health resorts succeed in recruiting participants for the regional programmes. A well-known barrier for the health professionals working in the resorts is that they are confronted with numerous patients, and that only a small number of them live in communities where regional exercise programmes are provided. As was found in other lifestyle programmes, the number of drop-outs or those lost to follow-up might be a limiting factor [40]. Due to the fact that the measurement of physical activity and its feedback in the preliminary studies was found to be appealing for the study participants, the number of drop-outs will hopefully be small. One factor which may be a slight limitation to the study is that people who quit the regional exercise programme or even never start it could also reach the weekly physical activity recommendation by being physically active independent of the regional exercise programme. Data from the questionnaire and information from the trainers will help to identify these cases.

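### Drop-out is treated only as a precision problem: six extra people per group cannot correct outcome-related loss, and by-visit ANCOVA makes no use of the 10-week MVPA of people missing at 12 months

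*Protocol article*

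**What the plan says.** All references are to the protocol article.

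- **Sample size calculation.** The inputs are a between-arm difference of 44.5 min in MVPA, an SD described as "a standard deviation of 72.2 MVPA of the differences", alpha 0.05 (two-sided) and 80 % power. They give 42 per group. The number is then raised to 48 because "drop-outs and those lost to follow-up may have an inestimable effect on the assumed standard deviation of the differences". No attrition rate is given, and no effect of drop-out other than on the standard deviation is mentioned.
- **Statistical analyses.** The group comparison is an ANCOVA adjusted for baseline, described as "comparing parameters after the intervention and after the follow-ups". Baseline is the only covariate named.
- **Measurements.** MVPA is measured in both arms before the stay, at 10 weeks and at 12 months, each time by seven consecutive days of accelerometer wear.
- **Intervention and Control group.** One arm receives a voucher for 12 trainer-led group sessions, offered twice a week. The other receives encouragement and a brochure.
- **Discussion.** The authors accept that "the number of drop-outs or those lost to follow-up might be a limiting factor" and hope the number will be small.
- **Eligibility and recruitment.** The stated total is 194 participants.

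**The concern.** Loss to follow-up does two separate things. It reduces the number analysed, which costs precision and which a larger sample can repair. If those who leave differ in activity from those who stay, it also shifts the mean of those who remain. No increase in sample size repairs that. The sample size rationale recognises only the first effect.

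The stated analysis does not address the second effect either. An ordinary ANCOVA of the 12-month value on arm and baseline contains only people with a 12-month value. The 10-week MVPA is collected in both arms and may be informative about who leaves and about their later activity, but it does not enter that estimate.

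The design makes unequal, activity-related loss plausible. The arms have different contact with the project, and the outcome needs a week of device wear, so providing it depends on motivation. At stake is the 12-month comparison of the primary outcome. If less active people leave, the arm that loses more looks better than it is. Loss of programme quitters would flatter the intervention, and loss of unmotivated controls would hide its effect.

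**Working it through.** **1. The plan's own figure.** Inputs from the sample size section: difference 44.5, SD 72.2, two-sided 0.05, power 80 %.

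n per group = 2 × (1.960 + 0.842)² × 72.2² / 44.5² = 41.3, rounded up to 42. The plan's figure reproduces. A t-test calculation gives 43, with power 79.7 % at 42.

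**2. What the six extra people buy.** 6/48 = 12.5 %, and 42/(1 − 0.125) = 48. The increase covers 12.5 % loss. Starting from 48 per group with the same loss in both arms, t-test power is:

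| Loss (assumed) | Power |
|---|---|
| 0 % | 84.8 % |
| 12.5 % | 79.7 % |
| 20 % | 75.5 % |
| 30 % | 70.7 % |

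If 194 is the enrolled number (97 per group, assuming equal arms), loss of 1 − 42/97 = 57 % would still leave 42 per group. The size of the allowance therefore depends on which total is right. In either case it is an allowance for numbers only.

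**3. Possible bias, loss driven by 10-week activity.** The documents give no loss rates or correlations, so all of these are assumed. The simulation has 400,000 people per arm, SD 72.2 and a true difference of 44.5. The correlation is 0.5 from baseline to 10 weeks and 0.5 or 0.7 from 10 weeks to 12 months. The log-odds of leaving after 10 weeks rise by 1 for each SD lower 10-week MVPA (odds ratio 2.7). Bias of the 12-month ANCOVA in people with a 12-month value:

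| Loss, intervention v control | Correlation 0.5 | Correlation 0.7 |
|---|---|---|
| 12.5 % v 12.5 % | 0.0 min | −0.2 min |
| 20 % v 10 % | +2.3 | +3.3 |
| 30 % v 10 % | +4.6 | +6.5 |
| 10 % v 30 % | −4.5 | −6.4 |

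Here baseline is linked to the 12-month value only through the 10-week value. A stronger direct link would make the bias somewhat smaller, because baseline adjustment would then recover more of it.

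An estimate that also uses the 10-week values of those who left is within 0.2 min of the truth throughout. That follows by construction, since loss was made to depend only on the 10-week value.

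**4. Possible bias, loss driven by the 12-month outcome itself.** Let the tendency to stay have correlation ρ with the baseline-adjusted 12-month residual (SD taken as 72.2), and let a fraction l be lost. The mean shift in those who stay is 72.2 × ρ × φ(z)/(1 − l), where z is the standard normal l-quantile and φ the normal density.

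- l = 30 %: 72.2 × 0.348/0.70 = 35.9, so ρ = 0.3 gives 10.8 and ρ = 0.5 gives 17.9 min.
- l = 10 %: 72.2 × 0.1755/0.90 = 14.1, so ρ = 0.3 gives 4.2 and ρ = 0.5 gives 7.0 min.
- Same ρ in both arms, 30 % against 10 %: 10.8 − 4.2 = 6.6 and 17.9 − 7.0 = 10.9 min. The sign reverses if the control arm loses more.
- ρ = 0 in both arms: no bias, however unequal the loss.
- Equal 12.5 % loss, outcome-related in the intervention arm only: 72.2 × 0.206/0.875 = 17.0, so 5.1 min at ρ = 0.3 and 8.5 min at ρ = 0.5.

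Unequal loss alone is therefore not enough to cause bias, and equal loss is no guarantee against it.

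**5. Scale.** The unadjusted standard error at 48 per group is 72.2 × √(2/48) = 14.7 min. A bias of 4.5 to 6.5 min is 10 % to 15 % of 44.5 and at most 6.5/14.7 = 0.44 of a standard error.

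**The case against.** The strongest objection is that this is a condensed article whose analysis plan is not shown. Rules for missing values and analysis sets commonly sit in such a plan, so their absence here is no fault. That stands, and the point does not rest on it. It rests on two things the article does state: a rationale that confines the effect of drop-out to the standard deviation, and a named method that, in its usual form, does not use the 10-week values at 12 months.

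Several stronger readings are tempting, and the text does not support them:

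- *The plan drops anyone who misses a visit.* The article does not say so. This is how an ordinary ANCOVA behaves, and the method could be run on imputed data.
- *The 12-month result will be biased.* It can be. Loss unrelated to the outcome given baseline produces none.
- *The attendance sub-groups contain only people who returned at 12 months.* The wording "At the 12-months follow-up, the intervention group will be divided into sub-groups for further analysis" gives the timing of the division and does not restrict it to returners. Attended sessions are counted separately in the process evaluation.
- *The six extra people are the only provision.* They are the only quantified allowance in the sample size section. The total of 194, the recorded reasons for leaving the programme and the acknowledged limitation also bear on attrition, although none of them corrects bias.
- *The 10-week measurement goes unused.* It has its own comparison and a stated purpose in the Discussion. It is only not shown to inform the 12-month estimate.

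The contrast in contact also fades. Twelve sessions at two a week take six weeks. After a stay of up to three weeks, a prompt starter finishes at about nine weeks, near the 10-week visit. Both arms follow the same activity measurement schedule, and the authors report that activity feedback appealed to participants in preliminary studies. Unequal loss is therefore plausible but not documented.

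**Conclusion.** The point holds in a limited form. The sample size section misdescribes what the extra participants can do, and the stated analysis makes less use of the collected data than a readily available alternative.

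The possible bias is modest under the assumed mechanism in which loss depends on 10-week activity, and it is well inside sampling error at the planned size. It is larger in some scenarios where loss follows the 12-month outcome itself, up to about 18 min when 30 % are lost and only the intervention arm's loss is outcome-related. Its direction cannot be known in advance. These sizes are illustrations and not forecasts. The change is worth making because it is cheap and bears on the primary outcome, and not because a large error has been shown.

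**What to change.** - **Statistical analyses.** For MVPA, replace the separate by-visit ANCOVAs with one mixed model for repeated measures, with baseline MVPA, arm, visit and arm-by-visit. Include everyone in the assigned group who has a baseline and at least one follow-up, whatever their session attendance. Read the 12-month difference from this model.
- **Sample size calculation.** State that the increase from 42 to 48 protects precision only, and that 6/48 corresponds to 12.5 % loss.
- **Eligibility and recruitment.** Reconcile the total of 194 with 2 × 48 = 96.
- **Reporting.** Give loss to outcome measurement by arm at each visit, so that readers can judge how far it was unequal.

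**Cost.** Wording changes and a little more analysis in the software already named, with no new visits or measurements. The downside is that the model assumes loss is explained by the observed values. If loss depends on activity after 10 weeks, some bias remains, and people with no follow-up at all are still excluded.
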